## Abstract

**Background:**

Nurses are in a key position to stimulate older people to maximize their functional activity and independence. However, nurses still often work in a task-oriented manner and tend to take over tasks unnecessarily. It is evident to support nurses to focus on the capabilities of older people and provide care assistance only when required. Function-Focused Care (FFC) is a holistic care-philosophy aiming to support nurses to deliver care in which functioning and independence of older people is optimized. Dutch and internationally developed FFC-based interventions often lack effectiveness in changing nurses’ and client’s behavior. Process-evaluations have yielded lessons and implications resulting in the development of an advanced generic FFC-program: the ‘SELF-program’. The SELF-program aims to improve activity stimulation behavior of nurses in long-term care services, and with that optimize levels of self-reliance in activities of daily living (ADL) in geriatric clients. The innovative character of the SELF-program lies for example in the application of extended behavior change theory, its interactive nature, and tailoring its components to setting-specific elements and needs of its participants. This paper describes the outline, content and theoretical background of the SELF-program. Subsequently, this paper describes a protocol for the assessment of the program’s effect, economic and process-evaluation in a two-arm (SELF-program vs care as usual) multicenter cluster-randomized trial (CRT).

**Method:**

The proposed CRT has three objectives, including getting insight into the program’s: (1) effectiveness regarding activity stimulation behavior of nurses and self-reliance in ADL of geriatric clients, and (2) cost-effectiveness from a societal perspective including assessments of quality of life and health-care use. Measurements will take place prior to program implementation (baseline), directly after (T1), and in long-term (T2). Parallel to the CRT, a process evaluation will be conducted to provide insight into the program’s: (3) feasibility regarding implementation, mechanisms of impact and contextual factors.

**Discussion:**

The SELF-program was developed following the Medical Research Council framework, which addresses the systematic development, feasibility testing, evaluation and implementation of complex interventions. The program has been subjected to a feasibility study before and results of studies described in this protocol are expected to be available from end 2022 onwards.

**Trial-registration:**

The study is registered in the Dutch Trial Register (NL9189), as of December 22 2020.

**Supplementary Information:**

The online version contains supplementary material available at 10.1186/s12912-022-00902-5.

## Background

Worldwide, predictions indicate that due to medical advances, the number of people aged ≥ 60 will double by 2050 from 12 to 22% [1, 2]. In the Netherlands, a similar increase is expected as the number of people aged ≥ 65 will increase most by 2060 and will account for one fourth of the total national population [3]. Although the aging of humanity is an optimistic development, it posits challenges for society, financial resources and a serious threat to people’s functional ability and independency [4–6]. Many people reach a point where formal care support to meet basic needs and complete activities of daily living (ADL) becomes inevitable. A significant goal and priority of the World Health Organization, and of national and local authorities worldwide, is to strengthen long-term care services and maximize the functional abilities and independence of older people [7, 8].

In the Netherlands, formal care support is provided by nursing care professionals and allied health professionals such as a physiotherapist en occupational therapist, throughout the entire care continuum [9–12]. For example, frail older people living at home or those residing in nursing homes are supported in ADLs such as personal hygiene and dressing, toileting, and nourishment [13, 14]. Given their direct and frequent contact, nurses are in a key position to stimulate and enable older people to maximize their activity, functional ability and independence. Despite their key role, nurses still often seem to work in a task-oriented manner and to – although well intended – take over tasks from clients unnecessarily [15]. For instance, recent observational work of den Ouden and colleagues showed that nurses took over ADLs in almost half of the cases and that nursing home residents remained inactive in over 50% of ADLs [16]. This is likely to deprive older people’s remaining abilities, impair their dignity and quality of life, and may ultimately lead to disability [17–19]. Although nurses generally do acknowledge their potential active role in promoting activity and self-perceive to have sufficient knowledge and recognize the benefits not only for their clients but also for themselves, various barriers seem to impede them to adequately support and enable older people to optimize their daily functioning [20–22]. For example, barriers may occur at the level of the client (e.g., lack of knowledge), the care worker (e.g., lack skills), the environment (e.g., narrow hallways), and the organization (e.g., lack of policy and support) [20, 22, 23]. For this reason, it is evident to foster programs that support nurses to adopt a proactive care attitude, to focus on the capabilities of older people, and to provide care support only when required.

Function-Focused Care (FFC) is a holistic care-philosophy that aims to support nurses to deliver care in which daily functioning and independence of clients is optimized. The key principle of FFC is that nurses are deemed to change from doing things ‘for’ the client, to encouraging clients to engage in functional and physical activity during all care interactions, taking into account their capabilities [19]. The principles of FFC-philosophy have guided the development of various (inter)national interventions for various care settings [24]. In general, such interventions have shown to be feasible in practice but have demonstrated mixed results regarding their effectiveness in improving care professionals’ activity stimulation behavior, and clients’ engagement in functional and physical activity [25].

Over the past decade, the Netherlands has built a considerable record regarding the systematic development of interventions based on the FFC- or related care philosophies in both long-term and acute care settings. Guided by the Medical Research Council (MRC) framework for complex interventions [26], divergent FFC-based interventions were developed, implemented and evaluated in Dutch long-term and acute care settings [27–30]. In line with internationally developed interventions, Dutch FFC-based programs showed equivocal results and thorough evaluations are suggested to improve future programs [25].

Syntheses from Dutch practices have provided valuable lessons learned and implications to optimize future programs and develop an advanced FFC-program, including: 1) the development of a generic FFC-program applicable to a variety of nursing care settings, which allows for tailoring to setting specific elements and needs of its participants, 2) addressing all FFC-components jointly instead of single elements, 3) the inclusion of a comprehensive interactive training component that provides ownership to its participants, 4) the incorporation of an extended integrated theory of behavior change, compared to the one addressed in the current philosophy, and 5) improvement of managerial support by ensuring sufficient time and staff resources [31]. These implications have led to the development of a renewed and advanced generic FFC-program, applicable to a variety of long-term care settings; the ‘SELF’-program. The program has recently been subjected to a feasibility and acceptability study in nursing home care, which yielded useful input from nurses for pre-implementation improvements.

The aim of the current paper is twofold: first the outline, content and theoretical background of the newly developed SELF-program are presented. Subsequently, we describe a comprehensive protocol for the assessment of the program’s effect, economic and process-evaluation among nurses and geriatric clients in a multicenter cluster-randomized trial.

## Methods and design

### SELF-progtram: outline and content

‘SELF’ is a Dutch acronym for *self-reliance, autonomy, life quality and functionality.* The ‘SELF’-program is a multi-component program based on the principles of Function Focused Care. The FFC-philosophy assumes a holistic approach in changing nurses’ care and consequently clients’ activity behavior, including (1) an assessment and revision of organizational policies and environment, (2) education of nurses, (3) the establishment of FFC-goals for clients, and (4) continued motivation and mentoring of nurses and clients [24].

The SELF-program is an embodiment of the FFC-philosophy and its components, and addresses all components in conjunction, including a comprehensive interactive training program as its core component. In addition, the SELF-program takes into account the lessons learned and implications from previous practices, meaning that SELF is applicable to a variety of nursing care settings, allows for setting- and context specific tailoring and needs of its participants, incorporates extended integrated theory of behavior change, and improves managerial support. The ultimate aim of the SELF-program is to improve activity stimulation behavior of nurses in long-term care services, and with that optimize levels of self-reliance in ADL in geriatric clients. The SELF-program is theoretically grounded in the Integrated Change Model for explaining and changing health-related behavior [32].

### Theoretical background

Nurses are deemed to change their own daily care behavior towards stimulating and enabling clients to – in turn – optimize their active involvement and self-reliance in ADL. Therefore, a sequential dual behavior change process is incorporated in the SELF-program. The dual sequential behavior change process forms the basis throughout the SELF-program and intends to primarily increase awareness, motivation and willingness in nurses to stimulate clients, where after nurses are trained to improve client’s activity behavior.

The FFC-philosophy assumes that in order to improve nurses’ stimulation behavior, one’s self-efficacy and outcome expectations of the desired behavior need to be enhanced [24]. While in fact these are two well-known determinants of a deliberate process of behavior change, integrative models of behavior change such as the Integrated Change Model (ICM), and implications from recent work suggest to address a broader spectrum of behavior change determinants and behavior change phases [32]. The ICM (Fig. 1) assumes that behavior change is not merely the result of being confident in one’s own abilities and viewing positive outcome expectations. By integrating various well-known socio-cognitive theories [33, 34], and building on the core principles of the Theory of Planned Behaviour [35], the model assumes a phased behavior change process differentiating between an awareness, a motivation and an action-planning phase, influenced by information and preceding factors.

**Fig. 1 Fig1:**
[figure not shown]
The integrated change model [32]

The model assumes that behavior change is a result of becoming aware of its necessity by activating risk perceptions and increasing knowledge of the desired behavior and its consequences. Moreover, a person’s cognizance level indicates if a person is (in)correctly aware of carrying out the desired behavior. From a behavior change perspective, creating awareness is an important prerequisite of enacting a behavior [36]. Subsequently, if sufficient awareness of behavior change is present, a weighing of the pros and cons (outcome expectations) of the desired behavior, perceptions of social influences, and the level of one’s own belief to successfully carry out the desired behavior (self-efficacy), determines the motivation to change someone holds. The strength of one’s intention or willingness to change a behavior is determined by these awareness and motivational factors. It is well known that expressing a high intention towards behavior change does not necessarily guarantee successful behavior change [37]. People who express a high intention towards behavior change have a higher likelihood of successful translation of this intention into practice, by performing action planning: preparing the behavior adequately and anticipating challenging situations by the formulation of coping plans. In this phase, self-efficacy again plays a key role in enacting these plans.

The action phase in the behavior change process of nurses overlaps with the cycle of behavioral change in their clients. To illustrate, once nurses establish a willingness to change, the action phase includes raising awareness, and motivating and enabling clients to optimize their self-reliance and time spend in ADL. However, the behavior change process for geriatric clients in the training component of the SELF-program is rather a mix between rational behavior change methods such as assumed in the ICM, and more unconscious and practical strategies, such as providing verbal cues [38]. This is so, because Dutch long-term care services include a mixture of geriatric clients with different somatic and psychogeriatric backgrounds, for which the combination of rational as well as unconscious behavior change methods may prove effective in enhancing self-reliance in functional activity more than rational methods alone.

### Outline of the SELF-program

First, the policy of the organization is assessed and if necessary reviewed whether the organization aims to provide care in which daily functioning and independence of frail older people is maximized. In case of absence of organizational policy, the SELF-program offers an example policy document to be discussed with and supplemented by the organizational board and team managers [24]. In line with recommendations of previous work, the SELF-program ensures that the policy is not only in place, but also adequately and repeatedly propagated to the nurses, e.g,. within the training component or team meetings [31]. Last, managerial visibility and support is encouraged to reinforce the desired behavior change among nurses.

The key component of the SELF-program is a comprehensive tailor-made training program, as staff training is considered a key-element in the desired change in day-to-day clinical behavior or nurses [22]. The training program consists of seven face-to-face sessions varying from one to two hours, spread over a period of three months, see Fig. 2. Each session consists of several interactive assignments, with a strong focus on bottom-up learning and autonomy to its participants. For instance, assignments are conducted in small groups with a subsequent plenary discussion. Sessions are guided by a trainer appointed from the organization, for example someone with a background in education or quality improvement. In addition, an assistant-trainer is appointed on a voluntary basis from the concerned care-team to provide the main trainer with adequate examples from daily care practice and to support the trainer in the conduct of the training sessions.

**Fig. 2 Fig2:**
[figure not shown]
Schematic overview of the SELF-program

Within the training program, the core components of the FFC-philosophy are addressed as well as an empathic focus on behavior change in nurses towards enhanced activity stimulation behavior. The training program starts with a two-hour kick-off session intended to increase awareness of activity stimulation behavior in nurses and to address and propagate the concerned organizational policy towards self-reliance and independence of clients. Predominantly, the kick-off session aims to map the starting point of the care team with regard to the willingness to improve their activity stimulation behavior. This way, the subsequent educational trajectory can be tailored to the needs from the care team in question. Based on triangulation, i.e., taking into account perspectives of the trainer, the manager of the care team and nurses themselves, a decision is made whether to continue with session 1 or 2 following the kick-off session. In case the team is insufficiently aware, motivated and willing to improve their function focused care behavior, the team will continue with session 1. On the contrary, if the team shows sufficient awareness of the necessity to change and willingness to improve their FFC-behavior, the team continues with session 2. In session 1, participants discuss awareness, attitudes and the necessity for behavior change towards enhanced activity stimulation behavior. Session 2 builds on session 1 by covering the topic of motivation and willingness to change behavior, as well as the essence of a consistent application of the intended behavior among care team members. Last, in session 2, one or more nurse champions (practice coaches) are appointed to ensure the intended behavior is adequately implemented in practice and to facilitate the ongoing motivation and mentoring of staff and clients after the training program has been completed [24, 39]. Session 3 is about translating the willingness into goals and concrete actions to facilitate actual behavior change. For instance, rational and practical tools are presented and discussed to pursue an optimization of functional activity and self-reliance in geriatric clients. Nurses are encouraged to exchange their experiences in encouraging functional activity in their geriatric clients. Compared to all other sessions, booster session 1 (midway) and booster session 2 (at the end) both last 1 h. Booster session 1 reviews the environment geriatric clients reside in, either in home care of in nursing homes and addresses viable options for adapting the environment. This element is supported by a checklist addressing relevant problem areas and potential environmental changes to optimize engagement in physical and functional activity, based on Resnick and colleagues [24]. Both booster sessions also intend to recap the content of the previous sessions to assure the nursing care team is actually ready to proceed to subsequent sessions. Session 4 is an actor-guided role-play session in which an external actor with expertise in healthcare is hired to practice activity stimulation behavior in a real-life and interactive manner. In session 5, attention is payed to behavior maintenance through continued motivation and mentoring of nurses and clients and by establishing concrete and tailored strategies and goals per client to encourage functional activity. Each session is concluded with a practical assignment to be discussed in the subsequent session.

### Study protocol for effect, economic and process-evaluation

To examine the effectiveness and cost-effectiveness of the SELF-program, a two-arm (SELF-program vs care as usual) multicenter cluster-randomized trial (CRT) will be conducted. The CRT has three objectives, including getting insight into the program’s: (1) effectiveness regarding activity stimulation behavior of nursing care professionals and in self-reliance in activities of daily living of geriatric clients (effect evaluation), (2) cost-effectiveness from a societal perspective including assessments of quality of life and health-care use (economic evaluation). Parallel to the CRT, a process evaluation will be conducted to provide insight into the program’s: (3) feasibility regarding implementation, its mechanisms of impact and contextual factors (process evaluation). The study was approved by the Medical Ethics Committee of the Zuyderland Hospital (METC-Zuyd; METCZ20210007). In line with Dutch regulation, no specific ethical approval was needed for this study according to the rules of the Medical Research Involving Human Subjects act (WMO) [40]. Amendments, if any, will again be submitted to the medical ethics committee. The study is registered in the Dutch Trial Register (NL9189). The protocol follows the evidence based recommendations addressed in the Standard Protocol Items Recommendations for Intervention Trials (SPIRIT) 2013 [41]. The SPIRIT-checklist is available as supplementary material to the trial protocol. The study recruitment commenced in spring 2021 and is expected to last until spring 2022. Data collection is expected to last until autumn 2022.

### Procedure and recruitment of participants

To examine the program’s effectiveness and cost-effectiveness, two participant groups will be recruited, i.e., nurses working in nursing home care and geriatric clients receiving nursing home care. Care organizations across the Netherlands are able to take part in the study as the SELF-program is widely disseminated through various (social) media platforms and national conferences. To be eligible to participate, organizations have to offer nursing home care. In case of organizational willingness to participate, formal approval of the board of directors will be requested and the client council will be informed about the study. In close agreement with organizational boards and team and location managers, nursing home wards will be selected to participate in the trial. Wards hosting somatic clients, as well as wards where psychogeriatric clients reside are eligible to be included in the study. Within an organization, dyads will be created consisting of two nursing home wards, which will then be pair-matched according to size and ward type, e.g., somatic or psychogeriatric ward. Of the two included wards from a dyad, one will be randomly allocated into the intervention group (SELF-program) or into the control group (care as usual), and clients residing at a ward will be allocated accordingly. Randomization will be conducted by means of computer-randomization using *random.org.* The unit of intervention will be the care ward, the unit of analysis will be the nursing care professional or the resident respectively.

To minimize the probability of contamination bias, dyads will be created of wards that do not collaborate in daily practice. In case of collaboration between wards, something likely to occur within nursing homes, randomization will take place on location level. Nursing home organizations in the Netherlands usually consist of multiple locations, which in turn consist of a varying number of wards. In the event of collaboration between wards within a location, the entire location is included in a dyad with a pair-matched comparator location. For example, a nursing home location with three collaborating psychogeriatric wards, will be pair-matched with a similar location.

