### Sample size calculation

Given the cluster-randomized trial design, the guidelines prescribed by Breukelen and Candel (2012) were applied for sample size calculation (N) [44]. The SELF-program is expected to induce a difference in groups’ averages of the primary outcome (the MAINtAIN-score), corresponding to a small to medium effect size of 0.4 (Cohen’s *d*). Further, the mean cluster size, i.e. the average number of nursing care professionals per ward, is estimated to be 15. Using the two-tailed t-test, with power and significance level of 80% and 5%, respectively, the required number of clusters (K) was then computed, using an interclass correlation coefficient of 0.05 to correct for the cluster-randomized design effect (DE), yielding K ~ 8. Subsequently, K was increased in 10% to adjust for differences cluster sizes, and the associated sample size was further augmented to account for a 20% attrition of care professionals between baseline and post-treatment. This yielded a total sample size of *N* = 330 (165 per arm) care professionals and geriatric clients in K = 22 nursing home wards, or 11 ‘dyads’. In order to achieve adequate participant enrolment, we aim to include > 22 nursing home wards.

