### Data analyses

#### Effect evaluation

Summary statistics of central tendency (mean, median) and dispersion (standard deviation, interquartile range) will be used for continuous variables, as appropriate, to describe the two groups, whereas categorical variables will be summarized by absolute count and relative percentages (%).

Effect evaluation will be conducted according to the intention-to-treat principle with mixed (multilevel) linear regression analyses to accommodate the hierarchical structure of the data: measurements are nested within individuals, which are nested within a ward. Both wards and subjects will constitute the random effects (three-level models). Treatment, time and, their interaction, capturing treatment vs. control average differences over time, will make up the relevant fixed-effects, together with background characteristics that will be included in the model as covariates. Outcomes will be standardized to be interpreted as effect sizes (Cohen’s *d*). The regression coefficient of the treatment*time interaction in the mixed linear regression analysis can, therefore, be interpreted as Cohen’s *d*. To establish which factors are linked to (a possible) differential attrition between the groups, a logistic regression analysis with be conducted. SPSS for Windows, version 27 will be used for all statistical analyses. The level of statistical significance will be set at 0.05 (using two-tailed tests). In case of significant interactions, subgroup analyses will be conducted to determine the differential effects. In case of unintended effects due to the intervention or due to the trial conduct, these will be reported accordingly.

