#### Economic evaluation

The economic evaluation will evaluate the cost-effectiveness of the SELF-program compared with care as usual over 6 months. The principal analysis will be the incremental cost per quality adjusted life year gained from the societal perspective using the EQ-5D-5L to calculate QALYs as recommended by the Dutch Healthcare Institute [45]. This will be calculated as the mean cost difference between the SELF-program and care as usual divided by the mean QALY difference to give the incremental cost-effectiveness ratio (ICER). Use of QALYs as a generic health outcome measure allows policymakers to compare cost-effectiveness results across different sectors to guide resource allocation decisions. Unit costs will be taken from the Dutch Manual for Costing in Economic Evaluations [49] and other standard published sources. The cost of the SELF-program will also include the costs related to the external actor, who is hired to guide the role-play session.

Estimates for mean total costs and QALYs’ incremental between the SELF-program compared with care as usual over 6 months will be derived using regression analysis to control for differences in baseline utilities and costs, as well as relevant stratification variables. A secondary analysis will include the cost per point change in the primary outcome measure (GARS-4) gained of the SELF-program compared with care as usual over 6 months. Where necessary, analyses will take into account clustering at the nursing home care level via random intercept models. Regression analysis will also be used in the secondary cost-effectiveness analysis to control for potential imbalances in baseline GARS-4 values and stratification variables. To quantify uncertainty around cost-effectiveness results, non-parametric bootstrap methods will be used and 95% bias-corrected and accelerated bootstrap confidence intervals will be calculated for the mean total cost and QALY/GARS-4 incremental estimates. The bootstrap replications will also be used to construct cost-effectiveness planes and cost-effectiveness acceptability curves, from which the probability that SELF-program is cost-effective compared to care as usual at 6 months of the trial will be computed for a range of values of the willingness to pay thresholds based on current recommendations [45].

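### Whole locations may be randomised, but the effect model and the sample size stop at the ward; the treatment*time standard error is too small if locations change differently over time

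*Protocol article*

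**What the plan says.** **Allocation** (Procedure and recruitment of participants). The default is a pair of wards: "Within an organization, dyads will be created consisting of two nursing home wards, which will then be pair-matched according to size and ward type". One member of each dyad receives the programme. If wards collaborate, the protocol changes the unit: "In case of collaboration between wards, something likely to occur within nursing homes, randomization will take place on location level". In that event "the entire location is included in a dyad with a pair-matched comparator location", and the illustration is that "a nursing home location with three collaborating psychogeriatric wards, will be pair-matched with a similar location".

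**Effect model** (Data analyses, Effect evaluation). The hierarchy is fixed: "measurements are nested within individuals, which are nested within a ward. Both wards and subjects will constitute the random effects (three-level models"). The effect estimate is the treatment*time coefficient. Location, organisation and dyad are not named; the covariates are unspecified background characteristics.

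**Sample size** (Sample size calculation). A two-tailed t-test with 15 nurses per ward and ICC 0.05 leads to 165 per arm: "care professionals and geriatric clients in K = 22 nursing home wards", which the text equates with 11 dyads.

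**Economic model** (Data analyses, Economic evaluation). Regression is used "to control for differences in baseline utilities and costs, as well as relevant stratification variables". Random intercepts at the level of nursing home care are added only if judged necessary.

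**The concern.** The unit of allocation and the top level of the analysis differ in a situation that the protocol itself calls likely. Three collaborating wards in one location share an allocation, and probably management and working habits too, yet they enter the model as three independent clusters. That is analysis below the randomised unit, and it can make the primary test reject too often. The sample size has the same gap, because 22 wards make 11 dyads only if every dyad is a pair of single wards. A protocol may leave the random effects to an analysis plan, but this one states them, and they do not match the allocation it describes.

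**Working it through.** **1. Wards and dyads.** Suppose two dyads are pairs of three-ward locations and five are pairs of single wards. Wards: 2×2×3 + 5×2 = 22. Dyads: 2 + 5 = 7, not 11.

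**2. The plan's sample size.** From K = 8 per arm the later steps reproduce: 8 × 1.1 × 15 = 132, and 132/0.8 = 165 per arm, or 11 wards. (The stated inputs give 98.1 × 1.70/15 = 11.1 wards per arm before inflation, not about 8. That is a separate matter and no evidence for this point.)

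**3. Design effect with location dyads.** Let w be the wards per location and π the share of the ICC at location level (not given in the documents; assumed).

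DE = 15 × [0.05πw + 0.05(1−π) + 0.95/15]

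- w = 1, the plan's case: 1 + 14 × 0.05 = 1.70
- w = 3, π = 0.5: 15 × (0.075 + 0.025) + 0.95 = 2.45
- w = 3, π = 1: 15 × 0.15 + 0.95 = 3.20

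Power for d = 0.4 with 165 per arm before attrition is Φ(0.4/√(2·DE/165) − 1.96):

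| DE | 0.4/SE | Power |
|---|---|---|
| 1.70 | 2.79 | 80% |
| 2.45 | 2.32 | 64% |
| 3.20 | 2.03 | 53% |

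With two wards per location, DE is 2.075 to 2.45 and power 71% to 64%. All these rows except DE 1.70 take every dyad to be a location dyad. They use the plan's own basis, a comparison of means.

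**4. The planned test.** The effect is treatment*time, taken here as baseline against one follow-up. Assumptions:

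- 12 nurses per ward (15 less 20% attrition)
- 12 wards per arm, in 6 two-ward or 4 three-ward locations
- residual variance 0.5 on the standardised scale
- location-by-time variance 0.01 and ward-by-time variance 0.01 at each time point

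With L locations and W wards per arm:

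- True variance = 4 × [0.01/L + 0.01/W + 0.5/(12W)]
- Planned model, which puts both time-varying parts into the residual: 4 × 0.52/(12W)
- Planned model plus ward-by-time: 4 × [0.02/W + 0.5/(12W)]

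Constant location, ward, dyad and subject intercepts do not appear in these formulas, because they cancel between baseline and follow-up. Without time-varying cluster variance, the true and model SEs agree (both 0.118; ratio 1.00).

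| | 6 × 2 wards | 4 × 3 wards |
|---|---|---|
| True SE | 0.1546 | 0.1650 |
| SE, planned model | 0.1202 | 0.1202 |
| Ratio; actual level of a 5% test | 1.29; 13% | 1.37; 15% |
| SE with ward-by-time added | 0.1434 | 0.1434 |
| Ratio; actual level of a 5% test | 1.08; 7% | 1.15; 9% |

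The actual level is 2 × [1 − Φ(1.96/ratio)].

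**5. Sensitivity.** With variances of 0.0125 each and 15 nurses per ward, the planned-model ratio is 1.42 to 1.54 (17% to 20%). With ward-by-time added it is 1.10 to 1.20 (7.5% to 10%).

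**6. Pairing.** A constant dyad effect also cancels (ratio 1.00). With dyad-by-time, ward-by-time and residual variances of 0.0125, 0.0125 and 0.5, 11 single-ward dyads, 15 nurses per ward, and ward-by-time in the model, leaving out the dyad gives a ratio of 0.89 and a level of about 2.7%. That is conservative.

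**The case against.** The strongest reply is that the primary coefficient is a treatment*time interaction, so a stable difference between locations drops out. This stands. A reader might compare ward means at one time point, find a type I error of about 8-15%, and take that as the error rate of the planned test. The documents do not support this, because no such comparison is planned. For the same reason, adding only a location or dyad intercept would leave the treatment*time SE essentially unchanged.

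Part of the inflation shown above comes from the missing ward-by-time term and would exist without any location dyads. This also stands. The location's own contribution is the smaller factor, 1.08 to 1.15.

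A reader might also infer that the standard errors are wrong in one known direction. They are not: omitting location can make them too small, while omitting the pairing tends to make them too large and costs efficiency rather than validity.

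Finally, the economic section does not ignore clustering, and the matching factors size and ward type are natural candidates for its stratification variables. What remains there is that the clustering is conditional and its level is not tied to the unit randomised. The aim of more than 22 wards softens the sample-size point but does not turn wards into dyads.

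**Conclusion.** The mismatch between the allocation and the stated analysis is explicit and should be fixed. It affects the primary test only if at least one location is randomised whole and locations change differently over time. The second is plausible when collaborating wards share practice, but the documents give no figure for it. Under the illustrative variances of 0.01 each, with all dyads at location level, a nominal 5% becomes about 13-15%, of which about 7-9% would remain once ward-by-time is modelled. With fewer location dyads or smaller variances the inflation shrinks. If no location is randomised whole, only the pairing remains, as an efficiency matter. The sample-size statement is open to correction in any case: its ward-to-dyad count and its design effect of 1.70 hold only for single-ward dyads.

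**What to change.** - **Effect model.** Define the cluster as the unit actually randomised: the ward, or the location where the location was allocated. Make it the top level, with a random effect that varies over time (cluster-by-time), and nest ward within it where a location has several wards. Include dyad with its time interaction, or the matching factors size and ward type.
- **Economic models.** Use the same randomised unit for clustering, unconditionally, and name the stratification variables as the dyad or the matching factors.
- **Sample size.** State the target in randomised units or dyads, and restate the power for the expected number of location dyads, giving the assumed share of the ICC at location level.

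The cost is small. The allocation identifiers already exist, so no data collection changes and only the wording of the model is affected. The downside is fewer degrees of freedom and a somewhat less favourable stated power.
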